### Inclusion criteria

In order to be eligible to participate in this study, a subject must meet all of the following criteria:Scheduled low complex lumbar spinal surgery defined as removal of intervertebral disc herniation, decompression of lumbar canal, and/or foraminal stenosis.Preoperative use of aspirinAge >18

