### Secondary objective

#### All separate primary outcomes individually

##### Absolute mean difference in operative blood loss between the study arms

Perioperative blood loss is determined by measuring blood recovered in the suction device during surgery and weighting of blood-saturated gauzes used during surgery. The Validated Intraoperative Bleeding Scale (VIBe scale) will be used in order to objectify the intraoperative bleeding severity [22]. All cases will receive a vacuum drainage system applied to the surgical wounds in order to record the postoperative blood loss in the first 24 h. Blood loss is registered in the hospital information system and recorded with a case record form that is to be filled out at the time of discharge from the hospital.

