## Statistical analysis

### Co-primary study parameter(s)

Statistical analysis will be performed using SPSS. The risk of hemorrhagic complications and reduction in thrombo-embolic perioperative events within 30 days after surgery will be compared by calculating the confidence intervals of both groups and noninferiority will be claimed if the complication risk percentage stays below 6.1 percentage points.

In order to compare the effect of predefined risk factors on the primary and secondary outcome (Table 2) a multivariate regression model with an intention to treat analysis will be used.

**Table 2 Tab2:** Predefined risk factors

Age	
Sex	
Type of operation Type of spinal procedure: non-instrumented decompression, fusion procedures, spinal level, degenerative, neoplastic	
Duration of surgery	
Amount of preoperative thrombocytes	
Prescribed aspirin dose (80 or 100 mg)	
Previous cardiac or cerebral infarctions (as well as coronary artery disease and transient ischemic attack)	
Duration of surgery	
Type of spinal surgery	

Additional outcomes will be the hemorrhagic outcome measures (perioperative blood loss, hemorrhage-related complications, need for reoperation, and transfusion requirement) that will be compared among both treatment groups with a chi-square or Student’s *t*-test. The treatment group bleeding risk is assumed to be below 0,0710 under the null hypothesis of inferiority.

Follow-up within the study ends at day 30 after surgery. All events after day 30 will not be registered for the Aspin trial. Incidental findings will be registered as well and assigned to the involved organ system.

In case of missing data, patients of the treating surgeon can be contacted to complete the missing information.

All efforts will be made to assemble data for the primary outcome analysis. In case this data is missing, participants will be excluded from the final analysis.

All patients randomized to one of the study arms will be analyzed according to the intention to treat analysis.

Missing data in baseline characteristics will be imputed using multiple imputation (*n*=10) based on the outcome and relevant baseline covariates using the “Multivariate Imputation by Chained Equations” (MICE) algorithm. Patients with missing primary outcomes will be excluded but every effort will be made to obtain follow-up.

The ACTS scale and PROMIS Global-10 score will be compared between pre- and postoperative assessment and between the study and control groups.

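### Perioperative blood loss is compared between arms by an unadjusted t-test although planned procedure and spinal level are available before surgery; adjusting for them would sharpen this secondary comparison modestly at no cost

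*Protocol article*

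**What the plan says.** All references are to the protocol article.

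- **Outcome.** The secondary outcomes include "Absolute mean difference in operative blood loss between the study arms", so the declared effect measure is a difference in means on the raw scale. On measurement the article states: "Perioperative blood loss is determined by measuring blood recovered in the suction device during surgery and weighting of blood-saturated gauzes used during surgery". A wound drain is also placed in all cases "in order to record the postoperative blood loss in the first 24 h". The article does not say whether the drain volume counts towards perioperative blood loss.
- **Arm comparison.** Under Co-primary study parameter(s), the additional outcomes are listed as "perioperative blood loss, hemorrhage-related complications, need for reoperation, and transfusion requirement", "that will be compared among both treatment groups with a chi-square or Student’s *t*-test". Blood loss is the one volume in that list, so the t-test is its test. No covariate is named.
- **Regression.** The same section plans a separate model: "In order to compare the effect of predefined risk factors on the primary and secondary outcome (Table 2) a multivariate regression model". Table 2 includes "Type of spinal procedure: non-instrumented decompression, fusion procedures, spinal level, degenerative, neoplastic" and also duration of surgery. Treatment arm is not mentioned as a term.
- **Procedures eligible now.** The Inclusion criteria define the surgery as "removal of intervertebral disc herniation, decompression of lumbar canal, and/or foraminal stenosis". Fusion is mentioned only for a possible extension of the study.

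**The concern.** Blood loss plausibly depends on which operation is done and at which level. Both are settled when the operation is scheduled, which is when randomisation takes place. A t-test leaves that between-procedure variation in the standard error. Adjusting for it changes neither the question nor the effect measure and normally narrows the interval.

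The planned regression does not clearly fill the gap. It is described as a study of risk factors and names no treatment effect. If it were used for the arm comparison as listed, it would condition on duration of surgery. That is measured after randomisation and could itself be lengthened by bleeding, so part of an aspirin effect could be adjusted away.

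What is at stake is precision on a secondary safety measure. That measure has some weight, because the planning rates imply few primary events: 277 × 0.01 + 277 × 0.03 = 2.77 + 8.31, or about 11. Blood loss gives a quantity in nearly every patient and so helps to show whether continuing aspirin increases bleeding.

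**Working it through.** **1. The plan's own figure.** The article gives a sample size only for the binary primary outcome. With rates of 1% and 3%, a margin of 6.1 points, one-sided 0.025 and the score test, the asymptotic requirement is 275.9, so 276 per arm. Power at 277 is 0.80 (0.81 by exact enumeration). The stated 277 per arm reproduces. Nothing comparable exists for blood loss, for which the article gives no mean, SD or expected difference.

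**2. Assumed inputs for blood loss.**
- 277 per arm (from the article); two-sided 5% (assumed).
- Two procedure types, half of patients each, with control means 1 and k, where k = 1.5 or 2.
- Lognormal volumes within procedure, with coefficient of variation c.
- Mean 20% higher with aspirin.

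**3. Approximate power by formula.**
- Within-procedure variance (control): W = c²(1 + k²)/2
- Between-procedure variance (control): B = (k − 1)²/4
- Mean difference: D = 0.2 × (1 + k)/2
- SE of the t-test: √[(W + B)(1 + 1.2²)/277]
- SE after adjustment: √[W(1 + 1.2²)/277]
- Power ≈ Φ(D/SE − 1.96)

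*k = 2, c = 0.75.* W = 0.5625 × 2.5 = 1.406; B = 0.25; D = 0.30.
- t-test: SE = √(1.656 × 2.44/277) = 0.1208; D/SE = 2.48; power ≈ Φ(0.52) = 70%.
- Adjusted: SE = √(1.406 × 2.44/277) = 0.1113; D/SE = 2.70; power ≈ Φ(0.74) = 77%.
- Interval width ratio: √(1.406/1.656) = 0.92, about 8% narrower.

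*k = 1.5, c = 1.0.* W = 1.625; B = 0.0625; D = 0.25.
- t-test: SE = √(1.6875 × 2.44/277) = 0.1219; D/SE = 2.05; power ≈ 54%.
- Adjusted: SE = √(1.625 × 2.44/277) = 0.1196; D/SE = 2.09; power ≈ 55%.
- Interval width ratio: √(1.625/1.6875) = 0.98, about 2% narrower.

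**4. Simulation, raw scale throughout (2,000 trials per row, Monte Carlo error about 1 point).**

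| c | k | t-test | adjusted for procedure |
|---|---|---|---|
| 0.5 | 1.5 | 97.8% | 98.9% |
| 0.5 | 2 | 92.2% | 97.6% |
| 0.75 | 1.5 | 78.2% | 81.2% |
| 0.75 | 2 | 71.8% | 77.2% |
| 1.0 | 1.5 | 55.2% | 57.2% |
| 1.0 | 2 | 50.3% | 55.2% |
| 1.5 | 1.5 | 29.0% | 29.5% |
| 1.5 | 2 | 27.4% | 27.8% |

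A separate run gave 71% to 78% (c = 0.75, k = 2) and 54% to 56% (c = 1.0, k = 1.5), in line with step 3. If procedures do not differ (k = 1), adjustment changes nothing (80.4% and 80.3% at c = 0.75).

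**5. Validity.** With no arm effect, the rejection rate was 4.2% to 5.5% for the t-test and 4.2% to 5.3% for the adjusted model, across c from 0.5 to 1.5.

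**6. Would a log scale be better?** That depends on how extra bleeding arises.
- If aspirin multiplies every patient's loss by 1.2, a log-scale t-test gains: at c = 1.0 and k = 1.5, 70.9% against 55.2%.
- If the same 20% rise in the mean comes from 10% of aspirin patients each losing an extra twice the mean, the ranking reverses: at c = 0.5 and k = 1.5, 93% for the raw t-test against 73% on the log scale. At c = 1.0 without procedure differences it is 59% against 47%.
- Raw-scale adjustment kept its gain of about 1 to 7 points under both patterns.

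**The case against.** The strongest defence is that the t-test is right for what the plan declares. The outcome is an absolute mean difference, the arms are equal and large, and type I error holds even with marked skew. That stands in full. A reader might infer that skewed volumes or unequal variances invalidate the test; nothing supports this.

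A second defence is that adjustment is already planned, since the regression covers secondary outcomes and lists procedure type. This stands in part: it would be wrong to say that the plan contains no covariate model for blood loss. But the text gives that model another purpose, does not name arm and includes a post-randomisation factor, while the arm comparison is assigned to the t-test. Further model detail may sit in an analysis plan that is not shown, but the choice of test is stated here.

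Third, the gain rests on assumptions. The article gives no blood-loss data, current eligibility is limited to low-complex surgery, and the cell-saver text refers to extensive procedures, so it is weak evidence of a heavy tail in this population. That stands, and it limits the point to a modest one.

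Other stronger readings are tempting but unsupported:
- **That the test should move to the log scale.** This replaces the declared difference in means with a ratio of geometric means and downweights the large losses that are the safety concern. Its advantage reverses when the excess sits in a minority of patients.
- **That blood loss is the only graded bleeding measure.** Drain loss over 24 h and an intraoperative bleeding scale are also recorded.
- **That a non-significant blood-loss result would count towards non-inferiority.** The claim is tied to the 6.1-point margin on complications.

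**Conclusion.** The point holds as a modest matter of efficiency. The stated arm comparison of blood loss ignores two pre-surgical factors that are already collected, and the other model in the section is not a sound substitute for an adjusted arm comparison.

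Under the assumptions above, adjusting the mean difference adds about 1 to 7 power points for coefficients of variation between 0.5 and 1.0. The gain is under 1 point at 1.5 and nil if procedures bleed alike. Spinal level was not modelled separately; any variation that it explains beyond procedure would add to the gain.

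The planned t-test is valid, and the primary non-inferiority conclusion does not depend on it. The change is worth making because it is free and keeps the declared effect measure.

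**What to change.** In the Statistical analysis section, take perioperative blood loss out of the t-test sentence and state instead:

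- Blood loss will be compared between arms with a linear model containing treatment arm, type of procedure and spinal level, both as planned before surgery. Duration of surgery will not be included.
- The result will be the absolute mean difference in ml, with a 95% confidence interval and test based on a robust variance.
- A ratio of geometric means from a log-scale model may be added as a supplementary summary. It does not carry the test.

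The procedure variable should separate disc removal from stenosis decompression, because the Table 2 categories as printed do not visibly do so. The Table 2 regression can stay as a description of risk factors.

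The cost is one or two sentences before database lock. No further patients are needed. The planned operation is already established at eligibility, so no new data should be needed either.

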### Interim analysis

No interim-analysis will be performed. Safety examination will be performed bij DSMB at 100 inclusions. The risk of life-threatening hemorrhagic complications and irreversible cardio- and/or neuro-vascular thrombo-embolic complications will be evaluated.

## Ethical considerations

### Regulation statement

The study will be conducted according to the principles of the Declaration of Helsinki (64th World Medical Association General Assembly, Fortaleza, Brasil, October 2013) and in accordance with the Medical Research Involving Human Subjects Act (WMO).

### Recruitment and consent

This study has been approved by the medical research ethics committee; in Dutch: Medisch Ethische Toetsingscommissie (METC). Participation in this study is on a voluntary basis. If persons do not wish to participate, they can do so without specifying. Deciding not to participate in the study will not affect regular treatment and follow-up care. Participants or guardians in case are allowed to withdraw from the study at any time after they have given their written consent.

Because all persons eligible for inclusion are aged 18 and older, all eligible subjects are legally competent to decide whether they wish to participate. Persons incompetent to decide, i.e., patients with severe cognitive dysfunction or psychiatric illness are excluded from participation in the proposed study.

On the consent form, participants will be asked if they agree to use of their data should they choose to withdraw from the trial. Participants will also be asked for permission for the research team to share relevant data with people from the Universities taking part in the research or from regulatory authorities, where relevant. This trial does not involve collecting biological specimens for storage

### Benefits and risks assessment and group relatedness

Participation in this study imposes no additional risk to patients. It is unclear whether the assumed risk for an increase in hemorrhage-related complications outweighs the risk of an increase in cardiac and neurologic thrombotic perioperative events. Currently, there is no consensus on whether or not aspirin should be discontinued before cranial or spinal surgery. Aspirin is typically discontinued in cranial and spinal surgery because of a potential increased risk of hemorrhagic complications. This again might delay surgical procedures and may carry the risk of resulting in an increase in cardiac and neurologic thrombotic perioperative events.

Furthermore, a DSMB will survey the safety of the continuation of aspirin perioperatively.

There are no further disadvantages of participating in this study. Outcome measurements are recorded during admission and regular outpatient visits, and thus, do not require additional visits to the hospital.

### Compensation for injury

The sponsor/investigator has liability insurance which is in accordance with article 7, subsection 6 of the WMO.

The sponsor (also) has insurance, which is in accordance with the legal requirements in the Netherlands (Article 7 WMO and the Measure regarding Compulsory Insurance for Clinical Research in Humans of 23 June 2003). This insurance provides cover for damage to research subjects through injury or death caused by the study.

€ 750,000 (i.e., seven hundred and fifty thousand Euro) for each subject who participates in the Research;€ 5,000,000 (i.e., five million Euro) in total for all damage incurred to all participants in all participating centers of the Research;€ 7,500,000 (i.e., seven million and five hundred thousand Euro) for the total damage incurred by the organization for all damage disclosed by scientific research for the Sponsor as “verrichter” in the meaning of said Act in each year of insurance coverage.

The insurance applies to the damage that becomes apparent during the study or within 4 years after the end of the study.

The insurance company of this research in the Haaglanden Medical Center:

Onderlinge Waarborgmaatschappij voor Instellingen in de Gezondheidszorg MediRisk B.A.[name] | [name]030 - 2027280 | www.medirisk.nlNL14ABNA0555074757Inschrijving K.v.K. Midden-Nederland 30110086 | vergunning AFM 12000611

## Administrative aspects, monitoring, and publication

### Handling and storage of data and documents

Data collection and checking for quality will be performed with a study data management system (CASTOR EDC). All research data will be accessible to the clinical investigator and to the research nurse per center only and will be stored for a duration of 15 years.

After inclusion, every patient will be blinded and randomized via CASTOR EDC. Only the name of the medical center and hospital identification number will be saved to retrieve patient data.

The handling of personal data will comply with the EU General Data Protection Regulation and the Dutch Act on Implementation of the General Data Protection Regulation. (in Dutch: Uitvoeringswet AVG, UAVG).

#### Public disclosure and publication policy

Research data can be presented or published in agreement with the principal investigator and project leaders only. No research data which can be traced to individual persons will be presented or published.

### Monitoring and quality assurance

The Trial Steering group is composed of the primary investigator and the senior coordinating investigators. This group evaluates the progress of the study per 2 months.

The study monitoring plan will be composed by the counseling HMC Science Committee. The risk classification of the Aspin study is assessed by the METC as negligible. For this, the NFU guideline is handled. According to this guideline, a yearly monitor visitation per participating center will be performed.

Furthermore, an assessment of the Data and Safety Monitoring Board (DSMB) will take place after each 100 participants completes their study participation. This will happen by supplying the DSMB with an update of the data up to that time point.

### Amendments

Amendments are changes made to the research after a favorable opinion by the accredited METC has been given. All amendments will be notified to the METC that gave a favorable opinion.

All substantial amendments will be notified to the METC and to the competent authority.

Non-substantial amendments will not be notified to the accredited METC and the competent authority, but will be recorded and filed by the sponsor.

### Annual progress report

The sponsor/investigator will submit a summary of the progress of the trial to the accredited METC and the HMC Science Committee (Wetenschapsbureau) once a year. Information will be provided on the date of inclusion of the first subject, the number of subjects included and the number of subjects that have completed the trial, serious adverse events/ serious adverse reactions, other problems, and amendments.

### Temporary halt and (prematurely) end of study report

The investigator/sponsor will notify the accredited METC of the end of the study within a period of 8 weeks. The end of the study is defined as the last patient’s last visit.

The sponsor will notify the METC immediately of a temporary halt of the study, including the reason of such an action.

In case the study is ended prematurely, the sponsor will notify the accredited METC within 15 days, including the reasons for the premature termination.

Within 1 year after the end of the study, the investigator/sponsor will submit a final study report with the results of the study, including any publications/abstracts of the study, to the accredited METC.

### Public disclosure and publication policy

The results of this study will be published in an international peer-reviewed scientific journal and will be presented at (inter)national scientific conferences and meetings. This will be in accordance with the CCMO statement of publication policy.

The datasets analyzed during the current study and statistical code are available from the corresponding author on reasonable request, as is the full protocol."

### Patient public involvement

The daily organization and support of this study is provided by the Science Commission of the Haaglanden Medical Center. In all the participating centers the Science Helpdesks will be involved as well, always with the support of the Science Commission of the Haaglanden Medical Center.

## Structured risk analysis

### Potential issues of concern

Level of knowledge about the mechanism of action

See chapter 1.b.Previous exposure of human beings to the test product(s) and/or products with a similar biological mechanism

Aspirin is a widely used and evidence-based medicament with an antithrombotic effect. The effect is based on an irreversible inhibition of thrombocyte aggregation. This is the effect of acetylation of cyclo-oxygenase in the thrombocyte by inhibiting the prostaglandin thromboxane A2.

As described in chapter 1 no evidence is available about the, assumed, increased risk of hemorrhage-related complication peri-operatively.c.Can the primary or secondary mechanism be induced in animals and/or in *ex-vivo* human cell material?

Not applicable.d.Selectivity of the mechanism to target tissue in animals and/or human beings

Not applicable.e.Analysis of potential effect

Not applicable.f.Pharmacokinetic considerations

Not applicableg.Study population

See chapter 4.h.Interaction with other products

Not applicable.i.Predictability of effect

Not applicable.j.Can effects be managed?

In case of complications related to the perioperative continuation of aspirin, thrombocyte transfusion can be considered and, if indicated, a reoperation in order to evacuate the hematoma. In order for complications to occur related to perioperative discontinuation of aspirin diagnosis and treatment will follow according to current protocolled guidelines.

### Synthesis

Aspirin is a medication, which is widely used. In situations of emergency surgeries, experience is available where surgeries are performed without discontinuation of aspirin. In case of hemorrhage-related indication, a thrombocyte transfusion can take place, where this is not the standard of care. This gives a point of view about the need to discontinue aspirin in elective low-complex lumbar surgeries. On the other hand, one of the goals of this study is to provide evidence for the reduction or a stable presence of cardiovascular and/or neurological thromboembolic events with no increase in risk present of hemorrhage-related complications. Concerning the overall risk of life-threatening or irreversible complications in the study populations, there is no rationale to support an increase in that risk.

The remaining risks of complications in the study groups are acceptable, because the complications are known risks and manageable complications with therapies that are standard of care in current protocols. This together with the profit of the reduction of thromboembolic events as mentioned earlier.

